#### Gender effects

The selected study population addresses possible gender effects. In our previous study on the Bc*l*l SNP effect in patients undergoing CS, 30 of 126 patients studied were female. Of these 30 women, 6 were homozygous and 24 were heterozygous or non-carriers of the SNP [12]. Even in this small subgroup, female homozygous carriers had significantly higher PTSD scores one week after discharge from the ICU than female heterozygous non-carriers (29.0 ±13.1 versus 16.2 ±6.7, *P* = 0.009). In the proposed study, out of 180 patients intended to be included (Figure 4), approximately 43 will be female. Assuming that the effect of the homozygous Bc*l*l *G SNP and the gender distribution in both study samples is identical, our study will be adequately powered to allow the detection of gender-specific effects of the intervention on post-traumatic stress one week after ICU discharge and at one year (primary endpoint).

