### Statistical analyses

#### Sample size calculations

In several previous studies in CS patients, we assessed post-traumatic stress using the PTSS-10 instrument that will also be the primary outcome measure in this study. Our preliminary work indicated an 8-point difference on the PTSS-10 scale between homozygous Bc*l*l *G carriers as opposed to non-carriers [12]. This study also showed that the PTSS-10 score did not significantly decrease until six months after surgery. We may assume that the non-trauma-focused control intervention does not change post-traumatic stress levels in homozygous patients and that the difference of 8 points in post-traumatic stress scores between non-carriers and homozygous individuals is clinically meaningful. This assumption is supported by the recent study discussed in the section *Primary endpoint*[26] that showed that even a relatively low PTSS-10 score (>20) in patients one week after ICU therapy and weaning from mechanical ventilation was highly predictive for the later development of PTSD. Based on the results of our pilot study [12], we make the following assumptions: first, the mean PTSS-10 score one year after ICU discharge is 18±8 (mean ±SD) for non-Bc*l*l *G carriers and heterozygous Bc*l*l *G carriers and 25±8 for homozygous Bc*l*l *G carriers each under control intervention. Second, the mean PTSS-10 score one year after ICU discharge is 18 ±8 for all patients under experimental intervention. Both assumptions show a quantitative intervention-SNP interaction. An overall sample size of 252 patients (84 per SNP group) is needed assuming a type I error rate of 5% and a type II error rate of 80% to detect a statistically significant differential treatment effect between the genotype groups. The sample size calculation was performed by Nquery (Statistical Solutions Ltd.,[name]). Further, experience from former studies shows a perioperative mortality of 8% and a loss to follow-up of approximately 20% of patients at the six-month time point [2,12]. Adjustment for a drop-out rate of 30% leads to a total of 120 required patients (120–0.3 × 120 = 84) per SNP group. In our previous study in 126 Western European CS patients from our institution, 43% were non-carriers of the Bc*l*l *G, 43% were heterozygous Bc*l*l *G carriers and 14% were homozygous [12]. This means that we will have to genetically screen approximately 872 patients to detect 120 homozygous individuals eligible for randomization. Genetic screening will also result in the identification of approximately 376 non-carriers and 376 heterozygous individuals. These patients will also be randomly allocated to the control and the targeted intervention group but, to reduce costs, only 120 individuals with each genotype will be randomly selected by choosing every third consecutive heterozygous or non-carrier patient included in the study. Thus, we will have to screen and genotype 872 patients to include 360 patients into the final analyses (Figure 4).

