#### Primary analysis

A two-factorial analysis of variance model will be used that includes the binary factor ‘intervention’ and a trinomial factor ‘genotype’. In a first step, an ‘interaction’ between both factors will be assessed. If this interaction exists in a second step, differential treatment effects will be tested between the three pairs of genotype groups. The global alpha level is guaranteed since the closed testing procedure will be invoked [43]. The primary data analysis set is the intention-to-treat population, which analyzes the data of the patients as they will have been randomized [44].

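### One SD of 8 in all six genotype-by-arm cells is not supported by the only observed genotype-specific SDs shown; plan for unequal variances and state power as a range

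*Protocol article*

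**What the plan says.** All from the Protocol article.

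- **Sample size calculations.** For non-carriers and heterozygotes under control, "the mean PTSS-10 score one year after ICU discharge is 18±8 (mean ±SD"). Homozygotes are set at "25±8 for homozygous Bc*l*l *G carriers each under control intervention". Under the intervention the assumption is "18 ±8 for all patients under experimental intervention". The section attributes these assumptions to the group's pilot study. They give 252 evaluable patients, 84 per genotype, "assuming a type I error rate of 5% and a type II error rate of 80"% (read here as a slip for 80% power). With 1:1 allocation that is 42 per cell.
- **Primary analysis.** "A two-factorial analysis of variance model will be used that includes the binary factor" for intervention and a three-level factor for genotype. The interaction is tested first, then differential effects between the three pairs of genotypes. No unequal-variance method is named. On error control: "The global alpha level is guaranteed since the closed testing procedure will be invoked".
- **Gender effects.** The same pilot study is quoted for 30 women one week after ICU discharge, 6 homozygous and 24 heterozygous or non-carriers: "29.0 ±13.1 versus 16.2 ±6.7". The P value printed there concerns the scores, not the SDs.

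**The concern.** The trial's main claim is a contrast between homozygotes and the rest. If homozygotes are more variable, a residual variance pooled over six equal cells is too small for any contrast that involves them and too large for the contrast that does not. Closed testing protects the global level only if each component test holds its own level, so the stated guarantee depends on the variance assumption. The sample size depends on it too, because the variance of the homozygous contrast is driven by the homozygous cells.

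The observed split points that way: the homozygous SD is about twice the other. The instrument gives some support to the direction. Its summary score cannot fall below 10, so a group centred on 18 has less room to spread than one centred on 25.

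**Working it through.** **Inputs.** Control means 18, 18 and 25; intervention means 18 in all genotypes; SD 8; two-sided 5% (sidedness assumed); 42 per cell (Sample size calculations). Observed SDs 13.1 (n = 6) and 6.7 (n = 24) (Gender effects).

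**1. The plan's own figure.** The homozygous-minus-non-carrier difference in treatment effect is (25 − 18) − (18 − 18) = 7. Its SE is 8 × √(4/42) = 2.469. Power = Φ(7/2.469 − 1.96) = 80.9%, or 80.6% with the t distribution. The stated 252 therefore reproduces as the size for one pairwise interaction contrast. The powers below refer to that same single contrast.

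**2. The observed SDs.**
- Variance ratio (13.1/6.7)² = 3.82 on 5 and 23 df; two-sided P = 0.023 under normality.
- Normal-theory 95% interval for the SD of 13.1: 8.2 to 32.1.
- Normal-theory 95% interval for the SD of 6.7: 5.2 to 9.4.
- Pooled SD of the 30 women: √[(5 × 13.1² + 23 × 6.7²)/28] = 8.2.

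**3. If 13.1 held in both homozygous cells and 6.7 in the other four.**
- Pooled variance: (2 × 171.61 + 4 × 44.89)/6 = 87.13. Pooled SE of any pairwise contrast: √(4 × 87.13/42) = 2.88.
- True SE, homozygous versus non-carrier: √[(2 × 171.61 + 2 × 44.89)/42] = 3.21. Actual level of the pooled test taken alone: about 7.7%.
- True SE, heterozygous versus non-carrier: √(4 × 44.89/42) = 2.07. Actual level: about 0.6%.
- Global interaction test, by simulation: level about 6%; power about 65%, against 84% with SD 8 throughout.

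**4. Power for 7 points with a valid SE**, Φ(7/SE − 1.96), 42 per cell:

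| Homozygous SD (control / intervention) | SD in other cells | SE | Power |
|---|---|---|---|
| 8 / 8 (plan) | 8 | 2.47 | 81% |
| 13.1 / 13.1 | 6.7 | 3.21 | 59% |
| 13.1 / 13.1 | 8 | 3.35 | 55% |
| 13.1 / 6.7 | 6.7 | 2.70 | 74% |
| 13.1 / 8 | 8 | 2.94 | 66% |
| 10 / 10 | 8 | 2.80 | about 70% |
| 8.2 / 8.2 | 6.7 | 2.31 | 86% |

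**5. The gated sequence, by simulation, SDs 13.1 and 6.7.** With no effect anywhere, the pooled procedure wrongly declares a homozygous-versus-non-carrier difference in just under 5% of trials. If only heterozygotes respond, strongly enough to open the gate, it does so in about 8%. Unequal-variance tests bring that back to about 5%.

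**The case against.** A reader might infer that the article's own data show the SDs to differ significantly, and hence that the error bars are wrong and the power is overstated. The documents do not support that.

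- **Population and time.** The SDs come from women only, at one week. The planned SD concerns both sexes at one year. The planning values of 8 per genotype are attributed to the whole pilot study, whose 12-month SDs by genotype are not shown.
- **The variance test.** It is not a result in the article. It rests on six patients and on normality, which a score with a floor at 10 makes doubtful. With equal variances but skewed scores (gamma, shape 1 to 4, an assumption), the nominal 5% test rejects 9% to 21% of the time.
- **Direction.** The pooled SD of these women is 8.2, close to the plan. With homozygous SD 8.2 and others 6.7, power is 86%. The floor argument supports a larger SD only in the homozygous control cell, because the plan puts treated homozygotes at 18 like everyone else.
- **Gating.** The pairwise tests are run only after the interaction test, so the 7.7% level does not apply when there is no effect anywhere.
- **Place.** A variance estimator is often left to an analysis plan, and ANOVA is a standard choice.

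Most of this stands, and it limits the point to a conditional one. Two parts do not remove it. The pooled 8.2 reflects 6 homozygotes in 30, whereas the trial makes them one third; the same two SDs then pool to √87.13 = 9.3. And the article does fix a single SD, a single power figure and a claim of guaranteed alpha.

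**Conclusion.** The common SD of 8 is an assumption that the one observed genotype split shown does not support. That split is too small, and too far from the endpoint, to show that the assumption is wrong.

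If the gap persisted in both arms, the consequences would matter: about 59% power with a valid SE, a homozygous contrast tested at about 8% when taken alone or when only heterozygotes respond, and an over-cautious heterozygous contrast. The effect on the global interaction test is modest, about 6% instead of 5%. It would go too far to say that overall error control fails outright.

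These figures assume 42 evaluable patients per cell and a true difference of 7 points; the levels and the simulations also assume normal scores. Power over the scenarios spans about 55% to 86%, so the single 80% figure could be wrong in either direction. The change is worth making because it costs almost nothing and removes the dependence of the tests on the variance assumption.

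**What to change.** 1. Keep the two-factor model and the gated closed testing. Base the interaction test, the three pairwise tests and their intervals on cell-specific or HC3 variances.
2. In the sample size section, replace the single 80% with power by homozygous SD (about 55% to 86% over the scenarios above), and cite the pilot's 12-month SDs by genotype if they are available.

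**Cost.** A small change in the analysis code and a sentence or short table in the text; no extra patients. If the variances are in fact equal, the loss is under one percentage point of power (global test 83.3% against 83.6% by simulation). The stated power would look less favourable at the upper end of the SD range.

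### Adequate power for gender-specific intervention effects is claimed from 180 patients, but neither 180 nor the planned 360 gives it at one year or for a difference between the sexes

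*Protocol article*

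**What the plan says.** Gender effects gives the number of women expected: "out of 180 patients intended to be included (Figure 4), approximately 43 will be female". The share comes from the earlier study, in which "30 of 126 patients studied were female". On genotype, the section reports: "Of these 30 women, 6 were homozygous and 24 were heterozygous or non-carriers of the SNP". Scores in homozygous women against the other women, one week after ICU discharge, were "29.0 ±13.1 versus 16.2 ±6.7, *P* = 0.009".

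The conclusion is conditional: "Assuming that the effect of the homozygous Bc*l*l *G SNP and the gender distribution in both study samples is identical", then "our study will be adequately powered to allow the detection of gender-specific effects of the intervention on post-traumatic stress one week after ICU discharge". The same sentence goes on to cover one year and names it as the primary endpoint.

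Sample size calculations gives a different total, citing the same Figure 4: "we will have to screen and genotype 872 patients to include 360 patients into the final analyses". The abstract agrees with that total (120 homozygous plus 240 other patients). The only power calculation in the article is for the intervention-by-genotype contrast with both sexes together.

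**The concern.** Two things do not fit. The patient number under the gender claim is half the number that the design includes. And the claim is about effects of the intervention by gender, while the evidence is a difference between genotypes, in six against 24 women, at one week. It involves no intervention and no comparison of women with men.

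A plan may leave subgroup power unstated. This one asserts it and ties it to the primary endpoint. A null result by sex could then be cited as adequately powered evidence of no difference, and a chance positive result as a planned, well-powered one.

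**Working it through.** **Inputs.** Share of women 30/126 = 23.8% (Gender effects). From Sample size calculations: 120 per genotype; 30% drop-out, leaving 84 per genotype and 252 in all; one-year mean 25 in GG controls and 18 under the intervention (7 points); SD 8. Allocation is 1:1 (Randomization). Assumptions: the 5% level is two-sided, and the printed type II error of 80% means 80% power.

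**The plan's own figures.**
- Women: 180 × 30/126 = 42.9, so the stated 43 does come from 180. With 360: 360 × 30/126 = 85.7, about 86.
- Sample size: with 42 per cell, the SE of the intervention-by-genotype contrast is 8·√(4/42) = 2.47. Then 7/2.47 = 2.84, and Φ(2.84 − 1.96) = 81%. The 252 reproduces and only just meets 80% with both sexes pooled.

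**One year, 360 randomised, 252 evaluable.** GG women: 84 × 30/126 = 20, or 10 per arm. GG men: 64, or 32 per arm.
- Intervention effect within GG women: SE = 8·√(2/10) = 3.58; 7/3.58 = 1.96; power 46% (t test; 50% by normal approximation). About 21 per arm would be needed for 80%.
- A 7-point sex difference in the GG effect: SE = 8·√(2/10 + 2/32) = 4.10; 7/4.10 = 1.71; power 39% (normal 40%). The difference detectable with 80% power is 2.8 × 4.10 = 11.5 points, more than the whole assumed effect.

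**Share of women among GG patients.** The trial fixes the number of GG patients, so the share of women among them matters. Six GG women out of about 18 (14% of 126) or about 21 (the 16.6% prevalence in the Background) is 33% or 29%. That gives 14 or 12 GG women per arm after drop-out.

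| One year, 7 points, SD 8 (t-based) | Within GG women | Sex difference in GG effect |
|---|---|---|
| 252 evaluable, 23.8% women | 46% | 39% |
| 252 evaluable, 29-33% women | 54-61% | 43-46% |
| 360, no drop-out, 23.8% women | 62% | 53% |
| 360, no drop-out, 33% women | 77% | 61% |
| 180, no drop-out, 23.8% women | 33% | 30% |
| 180 less 30% (126), 23.8% women | 23% | 22% |

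**One week, on the section's own condition.** Suppose that the intervention removes the full female difference, 29.0 − 16.2 = 12.8 points, and that 23.8% of GG patients are women.
- 360 less 30% (10 per arm): 72% with SDs 13.1 and 6.7 (Welch test, simulated); 92% with SD 8.
- 360 less 8% (assumption: only perioperative deaths are lost by then; 13 per arm): 84% and 98%.
- 180 less 30% (5 per arm): 37% and 60%. 180 with no loss (7 per arm): 53% and 79%.

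**Sex difference implied by the pilot.** Taking 8 points overall and 12.8 in women, with 18 GG patients, the effect in men is (8 × 18 − 12.8 × 6)/12 = 5.6, a sex difference of 7.2. With 21 GG patients it is 6.7. At 23.8% women, power is 37-41% with 252 patients, 46-51% with 331 (8% loss) and 49-55% with all 360.

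**The case against.** The protocol's premise is that the intervention brings homozygous patients to the level of the others. On that premise, the genotype difference in women is the assumed intervention effect in women, so the pilot data are a weak input but a relevant one. The stated condition at one week is 12.8 points, not 7. The 30% drop-out includes loss at six months and cannot all have occurred by one week. With 360 randomised, the one-week claim, read as an effect within GG women, is then defensible. All of this stands.

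Two further points also stand. The share of women among GG patients may exceed 23.8%, which raises the one-year figures. And no sex test appears in the primary or secondary analysis, so the sample size, the alpha and the main conclusion do not depend on the claim.

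A reader might infer more than the document supports: that power is 40-46% whatever the time point and effect, or that 180 is simply a slip for 360. The first holds only at one year, for GG patients, with 7 points, SD 8, 252 evaluable and 23.8% women. The second cannot be settled, because Figure 4, cited for both numbers, is not shown. 180 is half of 360 and may be a per-arm count, although the text presents it as the number to be included.

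**Conclusion.** The point holds in a limited form. The 180 conflicts with the 360 used elsewhere, and the claim of adequate power has no calculation behind it. At one year it is not met: about 46% within GG women (54-61% with the higher female share) and about 39-46% for a 7-point sex difference. No one-year scenario examined with the planning values reaches 80%; the best, with no drop-out and 33% women, gives 77% and 61%. For a difference between the sexes of about 7 points, the same shortfall applies at one week.

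What survives is narrower than the sentence in the protocol: a one-week effect within GG women, with 360 randomised and the whole 12.8 points removed (72-98%, depending on SD and early loss). At 23.8% women, the 180 stated in that section does not reach 80% even for this.

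The results assume a two-sided 5% level and rest on a female share drawn from small pilot counts. Because the primary analysis is untouched, this should be corrected but ranks below a must-fix.

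**What to change.** 1. Reconcile 180 patients and 43 women with 360 and about 86, and state whether the number is randomised, evaluable or per arm.
2. Withdraw the statement of adequate power, at minimum for one year and for differences between the sexes. If the one-week statement is kept, show its calculation: the effect, SDs, number of GG women per arm and expected loss.
3. State that gender-specific intervention effects are exploratory and will be reported as estimates with confidence intervals.

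The cost is wording only. The sample size, randomisation and primary analysis stay as they are; the protocol gives up a favourable property that it does not have.

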**Figure 4 F4:**
[figure not shown]
Flow chart depicting sample size estimation for the proposed study.

### Behavioral intervention to target traumatic memories and post-traumatic stress after surgery and intensive care unit treatment

The planned trauma-centered intervention will have an informative and resource-oriented approach to activate individual patient resources and cognitive (re)structuring to prepare for the oncoming surgery and subsequent ICU therapy. The major aim of the proposed intervention is to create realistic expectations about potential traumatic experiences that might occur, in order to render those experiences less surprising and hence reduce the subjective feeling of helplessness and distress in the patients. The intervention group will therefore be informed that some of them may have uncomfortable and potentially threatening experiences during the wake-up phase from anesthesia after heart surgery and while in the ICU. These potentially traumatic experiences could include nightmares and sometimes hallucinations or confusion, episodes of brief respiratory distress during weaning from mechanical ventilation, feelings of anxiety and some degree of pain from surgery. The study therapist will point out that these phenomena almost never occur during general anesthesia and heart surgery itself but are sometimes seen during the wake-up phase in the ICU after surgery. Participants will be told that these aversive experiences occur despite the best efforts of the therapeutic team in the ICU to avoid them by administering sedative and analgesic drugs in adequate dosages and the use of special techniques for extubation after mechanical ventilation. The therapist will also stress that these experiences usually do not indicate secondary complications after heart surgery and are generally self-limiting and of a temporary nature. The psychologist will further explore resources of the patient (for example, strategies that the patient had already successfully implemented to reduce stress, their social support networks, and future hopes and perspectives) and will encourage the patient to focus on these resources during and after ICU therapy. This information will be given to the patients in both written and oral form using simple and easily understandable language. A second part of the intervention is the provision of information about the context at the time of awakening, to orientate the patient in time and space directly after recovery from anesthesia. Likewise, the connection between sensory recollection about the potential traumatic experiences and autobiographical memories should be encouraged.

### Control intervention focusing on general aspects of psychological stress

To achieve significant differences between the trauma-focused ‘verum’ and the non-specific control intervention, the approaches need to be sufficiently different to avoid overlapping effects. The control intervention will therefore strictly avoid addressing the topics of ‘traumatic experiences or memories’ or ‘post-traumatic stress’ and, in contrast to the intervention group, no detailed information about the context of awakening will be given. Instead, the control group will receive information about the role of stress in heart disease and the possible benefits resulting from the use of stress management techniques in improving mental outcomes of CS. The control intervention will address questions regarding differences between normal daily stressors and pathological stress with dangerous health consequences, and why some individuals are more vulnerable to stress than others. It will also describe the relationship between pathological stress and an unhealthy lifestyle that results in an increased risk for heart disease. Furthermore, effective methods to reduce stress will be described to the patients. The patients will receive this information in both oral and written form. As during the specific intervention, all information will be given in a standardized and easily understandable manner.

